## 291 **7. Randomization**

292 A permuted block randomization method was used in this study. At each research center, consenting  
293 eligible participants were randomly assigned in a 1:1 ratio to the MSC group and control group using a  
294 computer-generated permuted block randomization schedule by statisticians who were not involved in  
295 the recruitment, treatment and therapeutic effect evaluation.. The permuted block size was randomly  
296 generated from among the numbers 4 and 6.

297 With permuted block of size four there are six possible patterns: AABB, ABAB, ABBA, BAAB,  
298 BABA, and BBAA.

299 With permuted block of size six there are 20 possible patterns:

AAABBB ABABAB BAAABB BABBAA

AABABB ABABBA BAABAB BBAAAB

AABBAB ABBAAB BAABBA BBAABA

AABBBA ABBABA BABAAB BBABAA

ABAABB ABBBAA BABABA BBBAAA

300

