| Research center          | Medical Center of Hematology, Xinqiao Hospital, Army Medical University
920th Hospital of Joint Logistics Support Force
The Affiliated Hospital of Guizhou Medical University
The General Hospital of Western Theater Command
The Third Xiangya Hospital of Central South University                                                                                                                                                                                                                                                                                                                                                         |
| Test purposes            | To explore the efficacy of umbilical cord-derived mesenchymal cells in preventing graft-versus-host disease (GVHD) after haploid-hematopoietic stem cell transplantation                                                                                                                                                                                                                                                                                                                                                                                                                                                                                 |
| Number of study cases    | 158 cases                                                                                                                                                                                                                                                                                                                                                                                                                                                                                                                                                                                                                                                |

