## 222     **6.1 Recruitment and Baseline Assessment**

223     Subjects who meet the conditions of 4.1 of this research protocol will undergo a series of functional  
224     examinations as necessary research indicators for clinical research. The physicians at the outpatient  
225     clinic who recruited patients did not participate in the randomization and treatment. The main  
226     examination items include but are not limited to the following examination items:

- 227     (1) Physical examination (weight, height, body surface area)
- 228     (2) Vital signs check: temperature, pulse, heart function check
- 229     (3) Routine blood tests: hemoglobin, white blood cells, platelets, etc.
- 230     (4) Liver and kidney function tests
- 231     (5) bone marrow imaging, bone marrow biopsy
- 232     (6) Leukemia residual disease (MRD), related gene mutation detection

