## 337 **11. Statistical Analysis Plan**

338 The Mann–Whitney tests, the chi-squared test, and Fisher's exact test were used to compare the AE  
339 between the MSC group and the control group. The competing risk model (Fine and Gray model) was  
340 used to estimate 2-year cumulative incidences and hazard ratios (HRs), with their 95% CIs, for severe  
341 cGVHD and cGVHD (competed by death and relapse) and leukemia relapse (competed by nonrelapse  
342 death). The cumulative incidence of grade II-IV aGVHD and grade III-IV aGVHD, the GRFS rate and  
343 the OS rate were estimated using Kaplan–Meier analysis and are expressed as percentages with 95%  
344 CIs. The Kaplan–Meier method, the log-rank test, and Cox proportional hazard models was used to  
345 compare the grade II-IV aGVHD and III-IV aGVHD, GRFS and OS curves between the two groups.  
346 All reported *P* values are two-sided. Statistical analyses were performed using STATA 17 (StataCorp.  
347 2021. Stata Statistical Software: Release 17. College Station, TX: StataCorp LLC)) and R (version  
348 4.4.2, R Foundation for Statistical Computing, Vienna, Austria).

349

350

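### Patients are randomised in blocks within each centre, but the analysis plan names no centre stratum; if centres differ in outcome, the tests are somewhat conservative and lose some power

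*Combined protocol and SAP*

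**What the plan says.** Section 7 (Randomization) states: "A permuted block randomization method was used in this study. At each research center, consenting" and continues "eligible participants were randomly assigned in a 1:1 ratio to the MSC group and control group using a" computer-generated schedule, with the block size "generated from among the numbers 4 and 6". The natural reading is a separate blocked list per centre. The synopsis lists five hospitals.

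Section 11 (Statistical Analysis Plan) assigns the Fine and Gray model to severe cGVHD, cGVHD and relapse: it is "used to estimate 2-year cumulative incidences and hazard ratios (HRs), with their 95% CIs, for severe" cGVHD and the other two outcomes. Kaplan–Meier, log-rank and Cox methods are to "compare the grade II-IV aGVHD and III-IV aGVHD, GRFS and OS curves between the two groups". No centre stratum, covariate, random effect or clustering term is named for any of these. Section 8 (Sample Size) plans on a log-rank test and does not mention stratification either.

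**The concern.** Blocking within centre keeps the arms nearly balanced in each hospital. An unstratified test computes its null variance as if the centre mix could still differ between arms by chance. If hospitals differ in event risk, that variance is too large for the design, and the test rejects a true null less often than 5%. If treatment works, the hazard ratio pooled over unlike centres is also pulled towards 1 relative to the within-centre ratio, which costs power.

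Differences between centres are plausible: the trial is open-label and chronic GVHD is graded clinically. There is also a specification issue. Because section 11 is silent on centre, a stratified and an unstratified result would both be available once the data are seen.

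**Working it through.** **Inputs from the documents.** N = 158, 79 per arm; 142/0.9 = 157.8, so the inflation for 10% loss to follow-up reproduces. The basis of the 142 is a separate matter and is not used here. Five centres; blocks of 4 or 6; 1:1; two-sided 5% tests; 2-year estimates. Severe cGVHD 15% (control) and 5.7% (MSC), from section 8. All-grade cGVHD 49.0% and 27.4% at 2 years, from the earlier study cited in section 1.1.

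**Assumptions.** The severe cGVHD rates are taken as 2-year risks, since section 8 gives no time point. Times are exponential, follow-up is 2 years and there are no competing events. Centre log hazards are normal with the SD shown.

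**Planning quantities.** Severe cGVHD hazard ratio = ln(1 − 0.057)/ln(1 − 0.15) = 0.0587/0.1625 = 0.361. Expected events = 79 × 0.15 + 79 × 0.057 = 11.9 + 4.5 = 16.4.

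**Tests compared.** Unstratified log-rank: Z = U/√V over all patients. Stratified: Z = ΣU_k/√ΣV_k, where U_k and V_k are the observed-minus-expected count and its variance within centre k.

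**Hand check under the null.** For a binary outcome balanced within equal centres, true variance over assumed variance is R = mean[p_k(1 − p_k)]/[p̄(1 − p̄)], and the actual level is 2Φ(−1.96/√R).
- Risks evenly spaced from 6% to 15%: p̄ = 0.105, variance of the p_k = 0.00101, R = 1 − 0.00101/0.0940 = 0.989, level 4.9%.
- Risks evenly spaced from 2% to 25%: p̄ = 0.135, variance 0.00661, R = 1 − 0.00661/0.1168 = 0.943, level 4.4%.

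**Simulation 1: severe cGVHD, the primary endpoint.** Centres of 60/34/28/20/16 patients (assumed), 6,000 trials per cell:

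| SD of log hazard | Type I error, unstratified / stratified | Power, unstratified / stratified |
|---|---|---|
| 0.3 | 4.7% / 4.8% | 50.8% / 51.0% |
| 0.6 | 4.4% / 4.9% | 53.0% / 54.1% |
| 0.9 | 3.9% / 5.2% | 54.6% / 57.9% |

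Power rises down the table because a larger spread around the same median hazard produces more events. The comparison that matters is within a row.

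**Simulation 2: GRFS-like endpoint.** Same centres; control hazard 0.35 per year, so 1 − exp(−0.7) = 50% fail by 2 years; hazard ratio 0.55 (assumed):

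| SD of log hazard | Type I error, unstratified | Power, unstratified / stratified |
|---|---|---|
| 0.3 | 4.4% | 65% / 66% |
| 0.6 | 3.8% | 62% / 67% |
| 0.9 | 2.9% | 56% / 68% |

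Stratified type I error was 5.0–5.1% throughout.

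**Simulation 3: five near-equal centres, average event count held roughly constant.** 8,000 trials per cell; Monte Carlo standard error about 0.24 points for type I error and 0.56 for power:

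| Endpoint | SD | Type I error, unstratified / stratified | Power, unstratified / stratified |
|---|---|---|---|
| Severe cGVHD | 0 | 5.0% / 4.9% | 48.4% / 48.4% |
| Severe cGVHD | 0.5 | 4.4% / 4.9% | 47.4% / 47.8% |
| Severe cGVHD | 1.0 | 4.1% / 4.7% | 41.4% / 44.6% |
| All-grade cGVHD | 0 | 5.5% / 5.5% | 81.6% / 81.0% |
| All-grade cGVHD | 0.3 | 4.3% / 4.8% | 79.5% / 80.4% |
| All-grade cGVHD | 0.5 | 4.4% / 5.3% | 76.3% / 79.0% |
| All-grade cGVHD | 1.0 | 3.2% / 5.1% | 59.7% / 70.1% |

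With SD 0, stratifying changes power by 0 and −0.6 points, which is about the simulation error.

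**What the SDs mean.** The expected range of five normal draws is 2.33 SD. The typical ratio of highest to lowest centre hazard is therefore exp(2.33 × 0.3) ≈ 2, exp(2.33 × 0.6) ≈ 4 and exp(2.33 × 0.9) ≈ 8.

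**The case against.** The strongest reply is that nothing in the documents shows that centres differ. One conditioning regimen and one prophylaxis regimen are specified for everyone, and no per-centre rates are given. The larger gains need four-fold or eight-fold differences in hazard between hospitals, and they arise on secondary endpoints. On the primary endpoint, with about 16 events, little is at stake. Section 11 is also silent on centre; it does not rule stratification out. All of this stands, and it limits the point to a conditional one about efficiency and specification.

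Two technical replies also stand. Stratifying does not shrink the standard error: in the GRFS-like runs at SD 0.9, log-rank information was slightly lower with strata (16.8 against 17.4). And the stratified hazard ratio is a within-centre quantity, not a marginal one.

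A reader might infer three stronger things that the documents do not support:
- That the trial's error rates are unsafe. Leaving centre out makes the test conservative; it creates no extra false positives.
- That stratifying would rescue the power. With the section 8 rates read as 2-year risks, 158 patients give about 48–54% power with or without centre, against the stated 90%.
- That baseline MRD, listed in section 6.1 as "Leukemia residual disease (MRD), related gene mutation detection", must also be adjusted for. It is not a randomisation factor, the documents give no cut-off or assay for it, and no gain has been computed.

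None of this removes the core: the design uses centre, the analysis plan does not say how centre is handled, and stratifying loses essentially nothing if centres turn out alike.

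**Conclusion.** The point holds in conditional form. Allocation is blocked within centre and no planned comparison names centre. If centre is prognostic, the unstratified tests are conservative. For severe cGVHD the loss is small: a power gain from stratifying of about 0, 1 to 2 and 3 points at SDs of 0.3, 0.6 and 0.9. For all-grade cGVHD and a GRFS-like endpoint it is about 0 to 1, 5 and 10 to 12 points, with type I error falling to about 3% at the largest spread. If centres do not differ, there is no loss.

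These sizes rest on assumed centre sizes and centre spread, 2-year risks, and log-rank tests without competing events. Competing death and relapse would reduce the severe cGVHD events further. This is a low-cost improvement to the plan, not a threat to its validity.

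**What to change.** Add to section 11 that between-arm time-to-event comparisons are stratified by centre: a stratified Fine and Gray model for severe cGVHD, cGVHD and relapse, and stratified log-rank and Cox analyses for aGVHD, GRFS and OS. Use strata, not a fixed effect per centre, because about 16 severe cGVHD events cannot support four extra coefficients. State in advance how small centres are pooled, from enrolment counts alone and without regard to arm or outcome. Report the unstratified result as a sensitivity analysis.

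The cost is wording only; centre is already recorded through the randomisation. There are two downsides to state. A centre with no severe cGVHD events contributes nothing to that test (on average about 0.4 of the five centres at SD 0.3). The hazard ratio must also be described as a within-centre one. The sample-size shortfall needs its own remedy.

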## 301 **8. Sample Size**

302 Sample-size estimates were based on the assumption of a log-rank test for the between-group  
303 comparison of the primary end point, the incidence of cGVHD. In the preliminary experiment, the  
304 cumulative incidence of severe cGVHD in the experimental and control group was 5.7% and 15%,  
305 respectively. We assumed 2 years for enrollment and 5 years for follow-up. A sample size of 142 total  
306 patients was calculated with a two-sided type II error of 0.05 and a statistical power of 90% for the

307 cumulative incidence of cGVHD. Considering the expected rate of loss to follow-up (10%), we decided  
308 to include 158 patients, with 79 patients in each arm. The sample size calculation was performed with  
309 PASS version 15 software (NCSS, Kaysville, UT).

310

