| Observation period       | (1) Real-time observation of the occurrence of acute and chronic GVHD after transplantation;
(2) Follow-up: relapse, death and HSCT related complication                                                                                                                                                                                                                                                                                                                                                                                                                                                                                              |
| Primary Endpoint         | Severe chronic GVHD                                                                                                                                                                                                                                                                                                                                                                                                                                                                                                                                                                                                                                      |
| Secondary Endpoint       | Chronic GVHD, acute GVHD, Overall survival (OS), GVHD-free and Relapse-free survival (GRFS).                                                                                                                                                                                                                                                                                                                                                                                                                                                                                                                                                             |

|                   |                                                                                            |
|-------------------|--------------------------------------------------------------------------------------------|
| Safety evaluation | Incidence of adverse events (AE) and severe AE during 45 days to 100 days after haplo-HSCT |
| Study period      | 2016.4-2022.2                                                                              |

29

30

31

32  
33  
34  
35  
36  
37  

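### Section 8 claims 90% power without a time horizon for 5.7% vs 15%; at section 11's 2-year horizon, power is about 44-54%, or 69-81% if those are 1-year rates

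*Combined protocol and SAP*

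**What the plan says.** Section 8 (Sample Size) opens: "Sample-size estimates were based on the assumption of a log-rank test for the between-group" "comparison of the primary end point, the incidence of cGVHD". The rates that follow are for the severe form: the "cumulative incidence of severe cGVHD in the experimental and control group was 5.7% and 15" per cent respectively, taken from a preliminary experiment. It continues: "We assumed 2 years for enrollment and 5 years for follow-up. A sample size of 142 total" "patients was calculated with a two-sided type II error of 0.05 and a statistical power of 90% for the" cumulative incidence of cGVHD. Allowing for 10% loss, 158 patients (79 per arm) are planned. No horizon for the two rates, no hazard ratio and no event count are given.

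Section 11 plans a Fine-Gray model, "used to estimate 2-year cumulative incidences and hazard ratios (HRs), with their 95% CIs, for severe" cGVHD and for all cGVHD, with death and relapse as competing events. The synopsis and section 2 make severe cGVHD the primary target. The synopsis gives the study period as "2016.4-2022.2". Section 1.1 reports 2-year cumulative incidences of all chronic GVHD of 27.4% and 49.0% from the centre's earlier trial.

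**The concern.** A log-rank test draws its power from the number of events. With 5.7% and 15% as the proportions affected, about 150 patients produce few events, far below what 90% power requires. The claim therefore depends on when those percentages apply and how long events are counted, and section 8 gives only part of that.

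The stakes are in interpretation. If the comparison is much weaker than stated, a non-significant result will be read as evidence of no benefit from a well-powered trial, when it should be reported as inconclusive.

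**Working it through.** **Inputs.** From section 8: 5.7% and 15%; two-sided 0.05, read as type I error; power 90%; 2 years of enrolment; 5 years of follow-up (total or additional is not said); N = 142, then 158. Allocation is 1:1 (section 7). The horizon of the rates is not stated, so I vary it.

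**Hazard ratio.** ln(1 − 0.057)/ln(1 − 0.15) = (−0.0587)/(−0.1625) = 0.361; ln 0.361 = −1.0185.

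**Events for 90% power.** (1.960 + 1.282)² = 10.51.
- Schoenfeld: 4 × 10.51/1.0185² = 40.5, so 41.
- Freedman: 10.51 × [(1 + 0.361)/(1 − 0.361)]² = 10.51 × 2.130² = 47.7, so 48.

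**Reproducing the plan's figure.** Take the rates as 1-year incidences (my assumption), with a constant hazard, uniform accrual over 2 years and 5 years in total. The event probability per arm is 1 − [exp(−3λ) − exp(−5λ)]/(2λ), with λ = 0.0587 and 0.1625. This gives 20.9% and 47.6%, mean 34.2%. Freedman: 48/0.342 = 140.3, so 141, or 142 with equal arms. At 142 there are 71 × (0.2088 + 0.4757) = 48.6 events and Freedman power 0.905. The inflation also agrees: 142/0.9 = 157.8, so 158.

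**Power by reading.** Schoenfeld power is Φ(√E × 1.0185/2 − 1.960); Freedman power is Φ(√E × 0.639/1.361 − 1.960), with E the expected events. Ranges run from Freedman to Schoenfeld. The 158 columns assume no loss.

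| Rates read as | Events counted | Events, 142 | Power, 142 | Events, 158 | Power, 158 |
|---|---|---|---|---|---|
| 2-year | to 2 years | 14.7 | 44-50% | 16.4 | 48-54% |
| 1-year | to 2 years | 27.6 | 69-76% | 30.7 | 74-81% |
| 2-year | 2-year accrual, 5-year total | 27.5 | 69-76% | 30.6 | 74-80% |
| 2-year | 2 + 5 years | 38.8 | 83-89% | 43.2 | 87-92% |
| 1-year | 2-year accrual, 5-year total | 48.6 | 91-94% | 54.1 | 93-96% |

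First row: 71 × (0.057 + 0.15) = 14.7 and 79 × 0.207 = 16.4. Second row: the 2-year incidences become 1 − 0.943² = 11.1% and 1 − 0.85² = 27.8%. Simulated log-rank tests agree: 44% and 49% for the first row, 73% and 77% for the second.

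**Precision in the first row, 79 per arm.** Expected events are 4.5 and 11.9. The standard error of the log hazard ratio is √(1/4.5 + 1/11.9) = 0.55, so the 95% CI around 0.361 is about 0.12 to 1.07. The equal-variance form, √(4/16.4) = 0.49, gives about 0.14 to 0.95. Either way the interval is very wide. On this reading, 90% power would need 41/0.1035 = 397 (Schoenfeld) to 48/0.1035 = 464 (Freedman) patients before loss.

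**What the reproducing reading requires.** It expects 47.6% severe cGVHD in controls over the follow-up, against 49.0% at 2 years for chronic GVHD of all grades in section 1.1. It also omits competing death and relapse. With an assumed combined competing hazard of 0.10 to 0.20 per year, the 48.6 events fall to 40.7 and 34.5, and power at 142 to 79-90%.

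**Calendar.** April 2016 to February 2022 is 70 months. That holds a 5-year total (60 months) but not 2 + 5 years (84 months).

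**The case against.** The strongest defence is that 142 follows from section 8's own inputs once the rates are read as 1-year incidences and the 5 years as total duration, and that this reading fits the calendar. That stands. A reader might infer that 142 is an arithmetic error, or that the trial simply has about 50% power. The documents support neither: nowhere are 5.7% and 15% called 2-year incidences, and linking them to section 11's horizon is an assumption.

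Nor does a constant hazard contradict the 15%. A rate of 15% at year 1 or 2 is compatible with a much higher figure later; the difficulty is plausibility, not logic. The calendar excludes only the 2 + 5 reading. It also does not cap power below 90%: over 70 months, 142 patients give 76-83% with 2-year rates but 94-97% with 1-year rates.

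Section 11 can be read with the 2-year limit applying to the incidences alone, leaving the hazard ratio to use all follow-up. It plans 95% CIs, which partly guards against misreading a null result.

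A second route to the sample size cannot be excluded. All cGVHD at 27.4% vs 49.0% at 2 years, with 2-year accrual and a 5-year total, gives a Freedman N of 140. That would not help: it would mean that power for the primary endpoint had not been calculated.

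**Conclusion.** The concern holds in conditional form. The 90% is unsupported at the only horizon the documents attach to severe cGVHD. For a comparison at 2 years, power is about 44-54% if the rates are 2-year incidences and 69-81% if they are 1-year incidences; neither reaches 90%. Power near or above 90% appears only when a constant hazard of severe cGVHD is carried to years 5 to 7 with no competing events.

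These figures rest on proportional hazards, equal arms, two-sided 0.05 and, at 158, no loss. Competing events that reduced the event count would lower those that extrapolate beyond the quoted rates.

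Three faults need no assumption: 0.05 is labelled a type II error beside 90% power, which implies a type II error of 0.10; the primary endpoint is named as cGVHD, not severe cGVHD; and a log-rank test is sized while section 11 plans Fine-Gray.

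**What to change.** Rewrite section 8 to state:

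- severe cGVHD as the endpoint sized, and a two-sided type I error of 0.05;
- the horizon to which 5.7% and 15% refer;
- the hazard assumption and the allowance for competing death and relapse;
- the expected number of events at 142 and at 158;
- power for the Gray or Fine-Gray comparison at the horizon actually analysed, in place of 90%. Expect about 44-54% for 2-year rates analysed at 2 years, and about 69-81% for 1-year rates analysed at 2 years;
- the expected width of the CI for the hazard ratio, with a statement that a non-significant result will be reported as inconclusive.

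If the hazard ratio is meant to use all follow-up, section 11 should say so, and the assumption "We assumed 2 years for enrollment and 5 years for follow-up" should be reconciled with the study period in the synopsis.

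The cost is rewording. No extra patients are needed; the downside is that the stated power becomes less favourable.
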